### Data collection

A series of measurements to assess back pain-related dysfunction, pain, quality of life and adverse experiences will be collected at baseline and week 1, 2, 3, 4, 8 and 12. At the screening visit, patients will be asked to fill out a questionnaire regarding their sociodemographic characteristics, including age, gender, marital status, residence, occupation and education level. A medical history will be also taken before their physical check-ups, and these factors will determine their eligibility for our study. Participation in can be ended at any stage if the patient refuses to continue or in the presence of significant clinical deterioration, as determined by the attending KMD researchers. For those participants who will be lost to follow-up and who drop out, intention-to-treat analysis will be applied to the existing data (Table 2).

**Table 2 T2:** Schedule for data collection: outcome measures per visit

**Measures**	**Baseline (Week 0)**	**Week 1**	**Week 2**	**Week 3**	**Week 4**	**Week 8**	**Week 12**
Sociodemographic characteristics	x						
Back pain history	x						
X-ray	x						
Visual analogue scale for bothersomeness of low back pain	x	x	x	x	x	x	x
Visual analogue scale for pain intensity of low back pain	x	x	x	x	x	x	x
Oswestry Disability Index	x	x	x	x	x	x	x
EuroQol-5D	x	x	x	x	x	x	x
Beck's Depression Inventory	x	x	x	x	x	x	x
Adverse experiences^a^		x	x	x	x		x
Credibility test^b^	x			x			

a. Adverse experiences : Any adverse experiences at any visit during treatment sessions and 12 weeks will be monitored. The research team will review all trial protocols, monitor patient safety and investigate any adverse events. b. Credibility test : The credibility of the real and sham treatments will be assessed using the validated Korean version of the credibility test.

#### Primary outcome measurements

Bothersomeness from LBP will be assessed using the 10-cm VAS for bothersomeness of LBP [18]. To evaluate the clinical severity and impact on activities of daily life in patients with CLBP, the VAS for bothersomeness is selected as a primary outcome measurement. Using the 10-cm VAS (0, absence of bothersomeness; 10, the worst bothersomeness imaginable), the patient will be asked to report the degree of bothersomeness from LBP within the past week. Bothersomeness of LBP will be measured at every single visit at baseline and 1-, 2-, 3-, 4-, 8- and 12-week follow-ups after beginning treatment. The primary end point is the third week follow-up, which marks the end of the six pharmacopuncture sessions.

#### Secondary outcome measurements

VAS for pain intensity: The pain intensity of LBP will be assessed using the 10-cm VAS for LBP [19,20]. This inventory is a fast and straightforward method for evaluating the subjective degree of pain. Pain intensity will be measured in the same fashion as VAS for bothersomeness (0, absence of pain; 10, the worst pain imaginable) at every single visit at baseline and 1-, 2-, 3-, 4-, 8- and 12-week follow-up visits after beginning treatment.

The Oswestry Disability Index (ODI): Back pain related dysfunction will be assessed using the ODI [21]. The ODI contains 10 questions about daily activities, including inventories of pain intensity, personal care, lifting, walking, sitting, standing, sleeping, sexual life, social life and traveling. Each question is rated on a scale from 0 to 5 points; the lower the score, the less disabled the person is by the pain. The validated Korean Version of the ODI [22] will be administered at baseline and 1-, 2-, 3-, 4-, 8- and 12-week follow-up visits after beginning treatment.

The EuroQol 5-Dimension (EQ-5D): Quality of life for patients with LBP will be assessed using the Korean version of the EQ-5D [23,24]. The EQ-5D includes generic questions about quality of life as it relates to personal health. This inventory has two parts. In the first part, tthe patient evaluates his or her health state with respect to five dimensions in a descriptive way: mobility, personal care, daily activities, pain or discomfort, and anxiety or depression. Each dimension is scored on a scale from 1 to 3; the lower the score, the better the state of health of the test taker. In the second part, the patient rates his or her overall state of health on the day the questionnaire is completed using a VAS scale from 0, which is the worst imaginable state of health, to 100, the best possible state of health. The two scores are complementary. The EQ-5D has an index of reference value of possible health profiles ranging from a value of 1 (the best state of health) to 0 (death). The EQ-5D will be administered at baseline and 1-, 2-, 3-, 4-, 8- and 12-week follow-up visits after treatment begins.

Beck’s Depression Inventory (BDI): Depressive symptoms from LBP will be assessed by the Korean version of BDI [25,26]. The BDI includes 21 items and is a self-administered questionnaire. Each item has a response format ranging from 0 to 3, giving a theoretical maximum score of 63. The BDI will be administered at baseline and 1-, 2-, 3-, 4-, 8- and 12-week follow-ups after beginning treatment.

Credibility test: The credibility of the real and sham treatments will be assessed using the validated Korean version of the credibility test at baseline and again at the end of treatment [27]. The participants will rate the credibility of the treatment by answering four questions on a numeric rating scale, with 0 being not at all and 6 for maximal agreement:

1. improvement expected;

2. recommendation to others;

3. treatment logical;

4. effective also for other diseases.

#### Safety

Any adverse experiences at any visit during the six treatment sessions will be monitored. The research team will review all trial protocols, monitor patient safety and investigate any adverse events, which are defined as treatment-related experiences.

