**Methods/design:**

This study is a randomized, double-blinded, sham-controlled clinical trial with two parallel arms. Fifty-four patients between 18 and 65 years of age with non-radicular chronic low back pain experiencing low back pain lasting for at least the previous three months and ≥4 points on a 10-cm visual analog scale for bothersomeness at the time of screening will be included in the study. Participants will be randomly allocated into the real or sham bee venom acupuncture groups and treated by the same protocol to minimize non-specific and placebo effects. Patients, assessors, acupuncturists and researchers who prepare the real or sham bee venom acupuncture experiments will be blinded to group allocation. All procedures, including the bee venom acupuncture increment protocol administered into predefined acupoints, are designed by a process of consensus with experts and previous researchers according to the Standards for Reporting Interventions in Clinical Trials of Acupuncture. Bothersomeness measured using a visual analogue scale will be the primary outcome. Back pain-related dysfunction, pain, quality of life, depressive symptoms and adverse experiences will be measured using the visual analogue scale for pain intensity, the Oswestry Disability Index, the EuroQol 5-Dimension, and the Beck’s Depression Inventory. These measures will be recorded at baseline and 1, 2, 3, 4, 8 and 12 weeks.

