### Description of all interventions and comparisons

#### Treatment details

Both the real and sham BVA groups will receive a total of six pharmacopuncture sessions over three weeks. In the BVA group, 26-gauge sterile disposable syringes (Noksipja, Seoul, Korea) containing bee venom diluted with normal saline (0.9% NaCl) will be used, whereas normal saline without bee venom with the same dose will be used in the sham BVA group. A skin hypersensitivity test will be performed on all the patients at LI 11 acupoints with subcutaneous injections of 0.05 ml of 1:20,000 bee venom preparation. Local swelling over 10 mm in diameter or redness over 20 mm in diameter will be considered positive reactions, and these patients will be excluded from this study. At the first pharmacopuncture session, all participants will receive a copy of the *Exercise Manual for Patients with Low Back Pain* from the spine center of KHUHGD and will be encouraged to exercise according to the manual during the entire treatment period. As a rescue therapy to minimize the risk of disease deterioration during the trial period, all the participants will be prescribed loxonin (Loxoprofen, 60 mg/tablet; Dong Wha Pharm Co., Ltd., Seoul, Korea) per os one tablet three times a day throughout the treatment period.

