### Data analysis

The statistical analysis will be performed in the principle of intention-to-treat analysis and per-protocol analysis. For the intention-to-treat analysis, data will be processed with the last observation carried forward method.

A homogeneity test of the baseline characteristics will be performed on both demographical and clinical data using a two-sample *t*-test for quantitative data and a chi-square test for qualitative data. The two-sample *t*-test will be used for the VAS to evaluate the bothersomeness of LBP at baseline and again at four weeks (primary endpoint) for the comparison of the two groups and to determine differences from baseline. For each outcome variable, an analysis of covariance will be performed on the data to adjust the baseline characteristics. Trends over time and time-by-treatment interactions will be explored using a repeated-measures analysis of variance. A chi-square test or a Fisher’s exact test will be performed to determine the difference between groups and the adverse effects, which will be recorded and described as frequency and percentage. All statistical analyses will be carried out with the Statistical Package for the Social Sciences (SPSS, Inc., Chicago, IL, USA) for Windows version 18.0, and a significance level of 0.05 will be used.

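### The Safety section builds relatedness into the definition of an adverse event, and the article gives conflicting times for collecting adverse events; both need to be settled before the arms are compared

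*Protocol article*

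**What the plan says.** **Definition.** The Safety section states that the research team will "investigate any adverse events, which are defined as treatment-related experiences". The sentence before it uses a wider term: "Any adverse experiences at any visit during the six treatment sessions will be monitored". Footnote a of Table 2 uses the wider term too. The Data analysis section brings in a third term: a chi-square or Fisher's exact test "will be performed to determine the difference between groups and the adverse effects", at a significance level of 0.05. The article does not say which of the three sets is tested, or who judges relatedness.

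**Timing.** The Safety section ties monitoring to the six treatment sessions. The Data collection text says that "adverse experiences will be collected at baseline and week 1, 2, 3, 4, 8 and 12". The Abstract names adverse experiences among its measures and says "These measures will be recorded at baseline and 1, 2, 3, 4, 8 and 12 weeks". In Table 2 the row for adverse experiences is marked at weeks 1, 2, 3, 4 and 12 and is blank at baseline and week 8. Footnote a to that row says "Any adverse experiences at any visit during treatment sessions and 12 weeks will be monitored".

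**The concern.** An adverse event is normally any unfavourable occurrence, and its cause is recorded as a separate attribute. Where relatedness is part of the definition, someone has to attribute the event before it counts. That is a particular hazard here. The Discussion accepts that pain, swelling, redness and itching from the venom could compromise blinding. A judge who has guessed the arm may call an event related after venom and the same event unrelated after saline. The planned test would then compare attribution as well as occurrence.

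The schedule is a separate defect. Staff cannot follow four different statements of when to ask about events, and the choice among them decides whether anything after the third week is captured. The Abstract and the Discussion both promise evidence on safety, so the comparison is one that readers will use.

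**Working it through.** The plan states no safety figure to reproduce. The check is a comparison of the text, plus one illustration on assumed rates.

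**1. Which events count?**

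| Place | Term | Restricted to related events? |
|---|---|---|
| Safety, first sentence | adverse experiences | no |
| Safety, second sentence | adverse events | yes, by definition |
| Data collection text; Table 2 and footnote a | adverse experiences | no |
| Data analysis | adverse effects | not stated |

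The only definition given is the restricted one, and the term that is tested is not defined.

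**2. When are events collected?**

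| Place | Baseline | Weeks 1, 2, 3 | Week 4 | Week 8 | Week 12 |
|---|---|---|---|---|---|
| Safety | no | yes | no | no | no |
| Data collection text; Abstract | yes | yes | yes | yes | yes |
| Table 2 row | blank | yes | yes | blank | yes |
| Table 2, footnote a | not stated | yes | unclear | unclear | yes |

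Under Treatment details, patients "will receive a total of six pharmacopuncture sessions over three weeks". On the Safety wording, monitoring therefore ends at about week 3 and leaves 12 − 3 = 9 of 12 weeks uncovered. On the Table 2 row, the longest interval between enquiries is 12 − 4 = 8 weeks. The repeated efficacy rows of the same table do carry a week-8 mark, so the blank does not look like a fault of text extraction.

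**3. What could an arm-dependent filter do?**

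Inputs: 27 per arm (Sample size determination) and a 0.05 level with Fisher's exact test, two-sided (Data analysis; the two-sided form is assumed). Assumptions not in the documents: the true proportion of patients with an event is p in both arms; every venom-arm event is judged related; a share f of sham-arm events is judged related.

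Chance of a significant result = Σ over a, b of Bin(a; 27, p) × Bin(b; 27, p·f), summed over the tables with Fisher p ≤ 0.05.

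| f | p = 15% | p = 30% | p = 50% |
|---|---|---|---|
| 1.00 | 1.4% | 2.5% | 2.2% |
| 0.75 | 1.9% | 5.1% | 8.8% |
| 0.50 | 4.0% | 15.9% | 37.3% |
| 0.25 | 9.2% | 42.0% | 80.5% |

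The true rates are equal throughout, so every significant result is false. At p = 30% and f = 0.5 the expected counts are 27 × 0.30 = 8.1 against 27 × 0.15 = 4.05.

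If the same share is dropped in both arms, no difference is created. At p = 30% with half the events dropped in each arm, both rates become 15%, and the chance is 1.4%. The bias needs a filter that differs by arm.

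**The case against.** Four objections deserve weight.

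- **All experiences may be recorded.** The Safety section monitors adverse experiences generally, and the relatedness wording attaches to the events the team will investigate. Relatedness may therefore be applied only after everything has been recorded. This stands as a possible reading. A reader might infer that unrelated events are certain to be lost and the comparison uninterpretable, and the documents do not support that. What remains is that the only definition given is the restricted one and the tested set is undefined.
- **Blinding is planned.** The Design section and the section on randomization and blinding provide for blinded assessors and acupuncturists, and the Discussion says only that blinding could be compromised. A reader might infer that attribution will differ by arm. The documents support only that it may.
- **Late events may be captured.** Every statement except the one in the Safety section reaches week 12. A reader might infer that the plan misses late events; that follows only if the Safety section governs. Under Table 2, week-12 questioning could still recover events from the preceding eight weeks, with weaker recall.
- **Loxoprofen events are not shown to be excluded.** The Design section describes both arms as injection plus pharmacotherapy, so an event due to the drug can be read as treatment-related. The text leaves this open.

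It might also be tempting to cite the rate that zero events among 27 patients would exclude. That limit comes from the size of the trial and does not measure events lost through this wording.

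**Conclusion.** The point holds as two defects of wording. First, the stated definition makes relatedness a condition of being an adverse event and sits beside two other, undefined terms. If it governs, the between-arm comparison is open to bias to the extent that attribution follows a guessed arm. The size cannot be derived from the documents. On the assumed rates above, the false-positive chance stays near or below 9% at f = 0.75 and reaches 4% to 37% at f = 0.5. Second, the collection times contradict each other. That needs no assumption. Depending on which statement is followed, questioning stops with treatment, skips week 8, or runs through every visit to week 12.

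This should be corrected before the data are analysed. It does not show that events have been or will be lost, and it does not affect the primary efficacy comparison.

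**What to change.** 1. In the Safety section, define an adverse event as any unfavourable experience, whether or not it is thought related to treatment.
2. Record relatedness as a separate attribute, for the injection and for loxoprofen individually, judged by staff unaware of allocation. Visible skin reactions may still reveal the arm, which is why this judgement should not decide the main comparison.
3. In the Data analysis section, make all adverse events the main between-arm comparison and related events the secondary one, and use one term throughout.
4. List reactions to the skin hypersensitivity test separately and leave them out of the arm comparison. Under Treatment details every patient receives venom at that test, so counting those reactions would put venom effects into the sham arm.
5. Bring the Abstract, the Data collection text, Table 2 with footnote a, and the Safety section to one schedule that runs through week 12 and includes the existing week-8 visit. State whether anything is recorded at baseline, where the text and Table 2 now differ.

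The cost is revised wording in the protocol and case report form, slightly more recording, and one extra question at a visit that already takes place.

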### Withdrawal and dropout

Participation will be ended at any stage if the patient refuses to continue, withdraws consent, violates inclusion or exclusion criteria or the trial protocol, or completes less than four treatment sessions as determined by the attending KMD researchers. The trial will be stopped if the principle investigator believes that there are unacceptable risks of serious adverse events.

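### The withdrawal rule ends participation, not only treatment, on adherence and violation grounds, so the intention-to-treat analysis uses carried-forward scores where outcomes could have been observed

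*Protocol article*

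**What the plan says.** Withdrawal and dropout: "Participation will be ended at any stage if the patient refuses to continue, withdraws consent", and likewise if the patient "violates inclusion or exclusion criteria or the trial protocol, or completes less than four treatment sessions as determined by the attending KMD researchers". Refusal, consent withdrawal, violation and low attendance stand in one list with one consequence.

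Treatment details fixes the number of sessions: "Both the real and sham BVA groups will receive a total of six pharmacopuncture sessions over three weeks". Table 1 spreads them as two per week.

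Data collection covers those who leave: "For those participants who will be lost to follow-up and who drop out, intention-to-treat analysis will be applied to the existing data". Data analysis adds: "The statistical analysis will be performed in the principle of intention-to-treat analysis and per-protocol analysis", and then: "For the intention-to-treat analysis, data will be processed with the last observation carried forward method".

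Table 2 schedules the bothersomeness score at baseline and weeks 1, 2, 3, 4, 8 and 12. No section states whether a patient whose participation has been ended still attends these visits.

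**The concern.** Intention-to-treat needs the outcome of every randomised patient, whatever treatment was actually received. Here the protocol itself stops collecting outcomes in patients who attended poorly or breached the protocol, some of whom may be willing to keep completing questionnaires. Their later scores are then imputed by a single carried-forward value.

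What is at stake is bias more than precision. A score from baseline, week 1 or week 2 stands in for the end-of-treatment score, and the reason for the gap is tied to how treatment went. The Discussion accepts that pain, swelling, redness and itching specific to bee venom may appear in the active arm. The injected volume rises each week (0.2, 0.4, then 0.8 ml). If such reactions lead to missed sessions, the gaps would fall unevenly between arms. The attending doctors, who apply the rule, may also see those reactions.

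**Working it through.** **Step 1. What is ended.** The Withdrawal and dropout section ends participation. Data collection uses the same term for leaving the trial. No passage provides for follow-up off treatment.

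**Step 2. What happens to these patients in the analysis.** Data collection applies intention-to-treat to their existing data, and Data analysis fills the rest by last observation carried forward. They stay in the set, and collected data are kept.

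**Step 3. Which outcomes are lost.** Six sessions are planned, so the rule catches patients who complete 0 to 3, that is, who miss at least three. At two sessions a week, and if missed sessions are not made up (the document does not say), the third miss can come as early as the first session of week 2. The value carried to the primary time point is then the baseline, week 1 or week 2 score. A violation found after the primary assessment would cost only later visits. The loss depends on timing. (The primary time point is week 3 under Primary outcome measurements and week 4 under Data analysis; that is a separate inconsistency.)

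**Step 4. The plan's own figure.** Inputs from Sample size determination: difference 1.5, SD 2.73, power 0.80, alpha 0.05, attrition 20%, 27 per group. Two-sided normal approximation: n = 2 × (1.96 + 0.8416)² × 2.73² / 1.5² = 52 per group, and 52 / 0.8 = 65. The stated 27 is not reproduced. That is a separate defect and neither supports nor weakens this point. It does set the baseline power: SE = 2.73 × √(2/27) = 0.743, and power = Φ(1.5/0.743 − 1.96) = 0.52 (0.51 by the noncentral t).

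**Step 5. Illustration of size.** The document gives no share of patients ended by the rule, so these are assumptions. Let q be the share ended in each arm (equal in both) and r the fraction of the 1.5 cm difference held by their carried-forward scores. The expected difference is 1.5 × [1 − q(1 − r)]. With r from 0 to 0.5:

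| q | ended per arm (27q) | expected difference | power at 27 per arm |
|---|---|---|---|
| 5% | 1.4 | 1.43 to 1.46 | 0.48 to 0.50 |
| 10% | 2.7 | 1.35 to 1.43 | 0.44 to 0.48 |
| 20% | 5.4 | 1.20 to 1.35 | 0.37 to 0.44 |

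Not all of that fall is due to the rule. Patients with 0 to 3 sessions would probably not show the full effect if followed either. If r* is the fraction they would truly show, the error from carrying forward is 1.5 × q × (r − r*). With |r − r*| of 0.5 this is 0.04, 0.08 or 0.15 cm for q of 5%, 10% or 20%. At the extreme of 1 it is 0.08, 0.15 or 0.30 cm. The sign is unknown. With unequal shares by arm the error no longer takes this form and may go either way.

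**The case against.** The strongest reply is that the plan does keep these patients: they are analysed as randomised, with a stated imputation rule and a per-protocol analysis alongside. That is correct, and it rules out several stronger readings.

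- A reader might infer that outcomes are removed, or that the intention-to-treat result is close to a per-protocol one. The text supports neither. Collected data are kept, and a per-protocol set would leave these patients out.
- A reader might count 20% of 54 = 10.8 losses, suppose half are recovered by follow-up, and claim 24 instead of 22 per arm, with t-test power rising from 0.429 to 0.462. Those are complete-case figures. Under carry-forward all 27 per arm are analysed either way, so no such gain follows.
- A reader might state as fact that missingness differs by arm. The Discussion raises venom reactions only as a threat to blinding and does not link them to missed sessions. Treating staff are also meant to be blinded, although the Discussion accepts that this may fail. Possible is as far as the evidence goes.
- A reader might see exclusion after randomisation in the skin test, whose positives are subject to the words "and these patients will be excluded from this study" while the test is missing from the exclusion list and Table 2. But randomisation requires confirmed eligibility first, so the test most naturally precedes it. The Recruitment text is condensed and the study-sequence figure is not shown.

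What remains unanswered is that the rule ends participation and nothing provides for later outcome visits.

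**Conclusion.** The point holds as one about follow-up and missing data, not about exclusion from the analysis set. Followed as written, the rule replaces observable outcomes with carried-forward ones for an unknown number of patients, possibly including the primary outcome. On the assumed shares, the error in a 1.5 cm difference is modest, at most 0.30 cm when 20% of each arm is ended. The exposure to bias that differs by arm cannot be bounded from the document. The change should be made because it is cheap and removes a problem of the plan's own making; it does not invalidate the design.

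This rests on reading participation as including follow-up visits. If the full protocol keeps those visits going, only the wording needs correcting.

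**What to change.** Reword Withdrawal and dropout to separate stopping study treatment from leaving follow-up. Every randomised patient keeps all scheduled assessments to week 12 unless consent is withdrawn, and is analysed in the allocated group. Use the four-session and violation criteria only to define the per-protocol set that Data analysis already plans.

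Reconcile the two lists of grounds. Data collection says participation may be ended for refusal or clinical deterioration. Withdrawal and dropout makes ending mandatory, adds consent withdrawal, violation and low attendance, and omits deterioration. Which clinical grounds stop treatment is for the sponsor, and none is proposed here.

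As a clarity edit only, list the skin test among the exclusion criteria as completed before randomisation.

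Cost: protocol wording and a few more questionnaire visits, all already in Table 2. Patients who withdraw consent will still have missing data.
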